### Phase 3: Qualitative study (Interview)

**
*The aim of this part of the study is to explore patients’ experiences of participating in the study and understand any barriers or facilitators to retention and non-retention*
**

#### Objectives

•To identify and explore the reasons for patients choosing to participate in the study and their selection of taking part in the discontinuation or continuation group.•To capture experiences of study participation.•To identify the factors that facilitated retention of participants in the study.•To identify reasons why participants choose to withdraw from the study.•To explore participants’ views on the use of randomisation in future large-scale multi-centre study.

**
*Study Design: Descriptive qualitative methodology*
**

Using purposive sampling, 5–8 participants who completed the study, and similar number of participants who withdrew from phase 2 of the study, will be invited to participate in this phase. On completion of (or withdrawal from) phase 2 study, all participants will be given a PIS explaining this phase. Informed written consent will be taken and recorded. This will be reaffirmed when participants attend for their interview.

Participants will be offered a choice between face-to-face, telephone or virtual (via Microsoft Teams) interviews. These options were informed by advice from members of the PPAG, advice from researchers who had explored or worked on similar themes, literature suggesting that decliners would be reluctant to take part in face-to-face interviews,
^16^ evidence that well-planned telephone interviews can gather similarly rich data as face-to-face interviews,
^16^ and learning from the coronavirus pandemic. Interviewing will continue until saturation is reached, estimated around 12 informants.
^17^

A topic guide will be developed in consultation with the members of the PPAG and supervisory team. It is envisaged the interviews will explore the experience of participating in the study, the factors that influence the participants to complete or withdraw and the feelings of the participants regarding the use of randomisation in any future large-scale study. All interviews will be digitally recorded on a password protected device or software (e.g. Microsoft Teams) and transcribed verbatim by the chief investigator (subject to confidentiality and security of data transfer arrangements) in compliance with study centre’s data management policies. These data will be stored in the study centre’s secured and password protected server.

All transcribed interview data will be analysed using thematic analysis.
^18^
^,^
^19^ Transcripts will be imported in NVivo to facilitate data management. After familiarisation, reading and re-reading each transcript against sound file, coding will be undertaken. Sections of text will be named producing a list of codes. In collaboration with my supervisors, a thematic schema will be formed, which may initially undergo numerous stages of refinement, and ultimately produce an analysis of participants’ accounts.

### Study setting

Participants of the GAMBOL study (Phase 2 and Phase 3) will be identified, recruited, and assessed from the two endocrine outpatient clinics of the University Hospitals Birmingham NHS Foundation Trust listed below:
•Queen Elizabeth Hospital Birmingham•Birmingham Heartlands Hospital

### Eligibility criteria: Phase 2

Inclusion criteria:
•Patients aged 25 years and over with GHD.•GHD previously confirmed by a validated test as per guideline.
^7^
•On GH replacement therapy for 5 years or longer.•Able to provide informed written consent.•Receiving stable replacement therapy for other pituitary hormone deficiencies for at least 3 months prior to recruitment, unless adjustments are required for clinical reasons.

Exclusion criteria:
•Patients with poorly controlled diabetes (defined as having an recent HbA1c of >7%), poorly controlled hyperlipidaemia and severe cardiovascular disease.•Patients receiving treatment for low BMD or deemed to be requiring treatment for low BMD during baseline screening.•Patients who are unable to provide informed written consent.

### Eligibility criteria: Phase 3

Participants who completed phase 2 of the study and participants who withdrew (at any point) from phase 2 are eligible to take part in the phase 3 of the study.

### Sampling

**
*Size of sample*
**

As this is a feasibility study, a formal power calculation is not required.
^20^ A maximum of 25 patients in each group (50 in total) will be recruited in the phase 2 which is at the upper end of the numbers recommended for pilot/feasibility studies.
^21^ 5–8 participants who completed the phase 2, and similar number of participants who withdrew from phase 2, will be invited to participate in the phase 3 of the study.

**
*Sampling technique and recruitment*
**

Phase 2 (Observational Feasibility Cohort Study): purposive case sampling will be used to recruit study participants. Eligible patients will be identified from endocrine outpatient clinic lists and from the endocrine database of patients on growth hormone treatment. Patients who are willing to take part in the study will be given the choice of taking part in either the discontinuation group or the continuation group. Patients withdrawing from the discontinuation group will be invited to continue on the study for on-going monitoring.

Phase 3 (Qualitative Study: Interview): purposive sampling will be used to recruit study participant. Participants will be recruited from those taking part in the phase 2 of the GAMBOL study. Participants will be approached at the point of completing the phase 2 (study visit 5), whereas those who are withdrawing from phase 2 of the study will be approached at the point of withdrawal.

### Recruitment

**
*Sample identification (Phase 2)*
**

Participants will be identified from the following three primary sources:
I.By the clinical team through the outpatient endocrine clinic attendance at the Queen Elizabeth Hospital Birmingham and Birmingham Heartlands Hospital during patients’ routine follow-up appointment;II.By the chief investigator through the UHB endocrine database of patients on GH treatment, andIII.By the chief investigator from patients responding to advertisement posted on the UHB Trust research website and the Pituitary Foundation’s website and social media platforms.

**
*Sample identification (Phase 3)*
**

Two groups of participants will be recruited from those taking part in the phase 2 of the GAMBOL study. Those who completed the phase 2 will be approached at the point of completion (study visit 5), and those who are withdrawing from phase 2 will be approached at the point of withdrawal.

## Dissemination (Phase 2 and Phase 3)

The results of this study will be submitted as abstracts at national and international endocrine conferences and for publication in peer-reviewed journals. Results will be also disseminated to participants, with the support of the GAMBOL Study PPAG members, using a participant newsletter and through the Pituitary Foundation local and national meetings.

## Consent

Written and verbal consent will be obtained from all participants involved in the study by the chief investigator. A copy of the signed informed consent form (ICF) will be filed in the medical notes, and the original will be placed in the Investigator Site File (ISF). Patients who decline to take part in the study will be reassured that their care will continue in the endocrine clinic as planned.

## Withdrawing from the study

Any research participant can withdraw from the study (phase 2 or phase 3) at any point. Participants on the GH treatment discontinuation group who choose to withdraw from the study due to side effects and wish to restart GH treatment, will be invited to continue on the study, as part of study group 3, for on-going monitoring whilst they restart their treatment. This will allow monitoring if their symptoms improve following re-introduction of GH treatment. Only participants who consented will continue on the study.

Withdrawal can be made in person during the follow-up study visit, by phone or by email without the need to explain the reason for withdrawal. Withdrawal from the study will be documented on the patient’s clinical notes and patient’s GP, as well as the endocrine consultant, will be informed in writing.

## Ethical and regulatory considerations

**Ethics Reference Number:** HRA and Health and Care Research Wales (HCRW) Approval (23/WA/0105).

**Approval date:** 17 April 2023.

REC approval has been sought for the phase 2 and phase 3 of the GAMBOL study. The study will be performed in accordance with the recommendations from the ‘World Medical Association Declaration of Helsinki’, adopted by the 18th World Medical Association (WMA) General Assembly, Helsinki, Finland, 1964, amended by the 48th WMA General Assembly, Somerset West, Republic of South Africa, 199.

The study will also be conducted in accordance with the Research Governance Framework for Health and Social Care, the applicable UK Statutory Instruments, (which include the General Data Protection Regulation and Data Protection Act 2018 and Human Tissue Act 2008) and the principles of Good Clinical Practice (GCP).

Risk will be assessed and managed at each stage of the ethical review process. The overall risk to the study participants is low as no serious and long-lasting effects are expected.

### Assessment and management of risk

Risk will be assessed and managed at each stage of the ethical review process. UHB, as sponsor, has comprehensively reviewed the study protocol, before submission to the Research Ethics Committee, and will monitor the conduct of the study. UHB’s Research and Development (R&D) department has also reviewed and approved the study. The overall risk to the study participants is low as no serious and long-lasting effects are expected (as described in detail below).

The following risks are anticipated in the study:
a.Participants will undergo blood test procedure at each study visit. The site of venepuncture might bleed or bruise. These will be minimised by the use of good clinical practice and sterile techniques. To avoid subjecting participants to multiple invasive phlebotomy procedures, all baseline biochemical measures will be taken after eligibility is confirmed. The volume of blood to be taken at each visit would be maximum of 20 ml. It is safe losing this amount of blood at each attempt at venepuncture at each visit and there are no adverse effects to expect from this procedure.b.The participants will arrive fasted for their study visit but will be allowed to eat as soon as blood samples have been taken.c.If any of the routine baseline bloods are outside the normal range, the patient, their endocrinologist and their GP will be informed and further advice will be provided.d.Participants will be exposed to ionising radiation by undergoing DXA scan. DXA scan is used routinely in clinical practice to assess baseline bone density and body composition in adult patients with GHD. However, some study participants will receive additional radiation burden from the repeat scan at 24 months, which is above that anticipated in routine clinical care. In clinical practice, only those patients with abnormal baseline DXA scan undergo a repeat scan after 2–3 years to assess any further deterioration or response to treatment (if bone metabolism medication is started). In this study, all study participants will have a repeat DXA scan regardless of their baseline scan result. The risk of harm from the additional radiation burden is low and is justified to provide objective radiological assessment during the study. The scan will be performed using the GE Lunar iDXA scanner. The amount of ionising radiation that each participant will be exposed to during each DXA scan procedure is around 0.03 milliSieverts (mSv) (lumbar spine = 0.013 mSv; both hips = 0.009 mSv; whole body = 0.008 mSv) and equivalent to around 5 days of background radiation in the UK (Damilakis
*et al.* 2010. Eur Radiol (2010) 20 (11): 2707–2714). Each participant will undergo DXA scan procedure twice (at baseline and at 24 months) during the duration of the study. The total amount of ionising radiation from the two DXA scans is 0.06 mSv which is equivalent to 10 days of natural background radiation in the UK. The interval between baseline and repeat DXA scan at 24 months is in line with standard practice as per the sponsor’s guideline for DXA scan. Ionising radiation can cause cancer which manifests itself after many years or decades. The risk of developing cancer as a consequence of taking part in this study is 0.0003%, which is low. For comparison, the natural lifetime cancer incidence in the general population is about 50%. DXA scan will be performed by qualified DXA scan practitioner who will be practicing in accordance with sponsor’s clinical guideline and the Ionising Radiation Regulations 2017.e.Participants will be asked to complete three Quality of Life questionnaires at each study visit and a final end of study questionnaire. This might be inconvenient to them in terms of time. Questionnaires validated for adults with GHD have been selected which contains minimal amount of data that meet the research requirement and the time needed to complete these questionnaires have been factored in at each study visit.f.Participants in the discontinuation group will be asked to stop their GH treatment for 2 years. During the period of GH treatment discontinuation, some participants may experience symptoms of GHD. Patients reporting symptoms of GHD or any other adverse events will be assessed promptly and those who wish to restart their GH treatment will be re-started promptly, withdraw from the study and be transferred to standard care. The risks associated with GH treatment discontinuation will be minimised as follows:

•low mood- participants will be advised at the start of the study, supported and reinforced by the PIS and during each study visit, to contact the study team if they have concern regarding low mood. Prompt initiation of GH treatment will be offered to participants who wish to restart their treatment;•poor general well-being- participants will be advised at the start of the study, supported and reinforced by the PIS and during each study visit, to contact the study team if they have concern regarding poor general well-being. Prompt initiation of GH treatment will be offered to participants who wish to restart their treatment;•low energy levels- participants will be advised at the start of the study, supported and reinforced by the PIS and during each study visit, to contact the study team if they have concern regarding low energy level. Prompt initiation of GH treatment will be offered to participants who wish to restart their treatment;•reduced bone mineral density (BMD)- BMD will be measured at baseline and at 24-months. Existing national guideline (NOGG, 2017) on managing low BMD will be followed and patients who require further assessment will be referred to their GPs. Patients who require active intervention for low BMD (following baseline assessment) will be excluded from the study. Prompt initiation of GH treatment will be offered to participants who wish to restart their treatment;•increased body fat- body fat mass will be measured at baseline and at 24-months. The importance of active lifestyle measures (e.g., regular exercise and healthy-balanced diet) will be reinforced to all participants at the start of the study, supported by patient information sheet and during each study visit. Patients who require active intervention, following baseline assessment, will be excluded from the study. Prompt initiation of GH treatment will be offered to participants who wish to restart their treatment;•increased cholesterol levels- cholesterol levels will be measured at baseline and every 6 months for 2 years. Existing national guideline on managing high cholesterol level will be followed and patients who require further assessment will be referred to their GPs. Patients who require active intervention for high cholesterol levels, following baseline assessment, will be excluded from the study. Prompt initiation of GH treatment will be offered to participants who wish to restart their treatment;

g.During the study period, each participant will be required to attend a total of 5 study visits for adverse events assessment, blood sampling, completion of questionnaires and measurements of body composition. The total number of planned study visits has been limited to the minimum requirement for the study which will ensure safety and appropriate follow-up of each participant. Each study visit will take place at the participants’ usual site of care and standard travel cost will be reimbursed to reduce the financial burden of travel.

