#### Objectives

•To assess the rate of patient recruitment, retention and withdrawal.•To identify barriers for recruiting and retaining participants into the study.•To assess the suitability and acceptability for patients of the frequency of follow-up and assessment.•To assess the suitability and acceptability for patients of the QoL questionnaires.•To assess the study protocol including recruitment, biochemical monitoring, body composition monitoring, and QoL assessment.•To assess the safety of GH treatment discontinuation in adult patients with GHD.

**
*Study participants*
**

The study will recruit a total of three groups of adult patients with GHD (aged 25 years and over).
I.
**
*Group 1-
Discontinuation group*
**: 20–25 patients who have been on GH therapy for 5 years or longer and voluntarily agree to discontinue their GH treatment and be monitored for two years.II.
**
*Group 2-
Continuation group*
**: 20–25 patients who have been on GH therapy for 5 years or longer and voluntarily agree to take part in the study, where their GH treatment is continued and are monitored in the same way as the discontinuation group.III.
**
*Group 3-
Continuation group following initial discontinuation*
**: patients who were initially part of the discontinuation group (Group 1) and decided to withdraw from the study, due to adverse effects of GH discontinuation, and restart their treatment. Patients monitoring will continue in the same way as the continuation group for a total of two years from the time they initially enrolled in the study.

**
*Study Visits*
**

Visit 1

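### The risk section sends discontinuers who restart GH out of the study to standard care, while the group definitions, sampling and withdrawal sections provide for their continued follow-up as Group 3

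*Protocol article*

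**What the plan says.** The protocol article deals with a discontinuer who restarts GH in four places.

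- **Assessment and management of risk, item f.** The sentence covers participants off GH who report symptoms of GH deficiency or any other adverse event. It says that "those who wish to restart their GH treatment will be re-started promptly, withdraw from the study and be transferred to standard care". It mentions neither Group 3 nor an invitation to stay.
- **Phase 2, Study participants, Group 3.** These are Group 1 patients who "decided to withdraw from the study, due to adverse effects of GH discontinuation, and restart their treatment". Their follow-up is explicit: "Patients monitoring will continue in the same way as the continuation group for a total of two years from the time they initially enrolled".
- **Sampling technique and recruitment.** Patients who leave the discontinuation group are invited to remain on the study for monitoring.
- **Withdrawing from the study.** The rule here concerns discontinuers "who choose to withdraw from the study due to side effects and wish to restart GH treatment". Of these people the section says that they "will be invited to continue on the study, as part of study group 3, for on-going monitoring whilst they restart their treatment". The reason given is: "This will allow monitoring if their symptoms improve following re-introduction of GH treatment". A condition follows: "Only participants who consented will continue on the study".

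The first Phase 2 objective is: "To assess the rate of patient recruitment, retention and withdrawal".

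**The concern.** Item f and the other three sections give opposite instructions for the same event. Staff who act on item f would discharge from study follow-up the participants who tolerated discontinuation worst. Those are the people for whom Group 3 was created. Their later quality-of-life scores, bloods, anthropometry and final DXA would be missing for a reason directly tied to how they fared off GH.

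A smaller, separate point concerns vocabulary. The Group 3 definition and the withdrawal section both speak of withdrawing from the study when describing people who may remain in it. Such a person can be read as retained or as a withdrawal under the first Phase 2 objective.

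**Working it through.** **1. Are these the same patients?** Item f is triggered by symptoms of GH deficiency or other adverse events, followed by a wish to restart. Group 3 is triggered by adverse effects of discontinuation plus restart, and the withdrawal section by side effects plus a wish to restart. The Adverse events section includes symptoms of GH deficiency among the occurrences reportable as adverse events. The populations therefore coincide for anyone who restarts because of how they feel off GH.

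**2. Does any sentence reconcile the rules?** The consent condition in the withdrawal section makes item f correct for those who decline to stay. Item f, however, is written for all who wish to restart and offers no alternative. Applied literally, it would leave Group 3 empty.

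**3. What is lost per restarter under item f?** Study Visits places visits at months 0, 6, 12, 18 and 24, with DXA at months 0 and 24 only. Scheduled visits lost are those falling after the restart:

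| Restart | Visits lost | Month-24 DXA lost |
|---|---|---|
| Before month 6 | 4 (6, 12, 18, 24) | yes |
| Months 6 to 12 | 3 (12, 18, 24) | yes |
| Months 12 to 18 | 2 (18, 24) | yes |
| After month 18 | 1 (24) | yes |

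Standard care would not reliably supply the scan. Item d of the risk section says that routine repeat DXA is for abnormal baseline scans only, and Eligibility criteria: Phase 2 already excludes patients needing treatment for low BMD. Follow-up of the adverse event itself is not lost, because the Adverse events section follows related events that lead to withdrawal until they resolve.

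**4. How far can the label move retention?** Group sizes are 20 to 25 each (Study participants; Sampling), so the cohort is 40 to 50. One Group 3 member counted as retained or as withdrawn shifts retention by 1/n:

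- discontinuation group: 1/25 = 4.0 points to 1/20 = 5.0 points;
- whole cohort: 1/50 = 2.0 points to 1/40 = 2.5 points.

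Illustration only, since the number who restart and stay is not given. Three such people give 3/25 = 12 to 3/20 = 15 points within the group, or 3/50 = 6 to 3/40 = 7.5 points over the cohort. Five give 20 to 25 points, or 10 to 12.5 points.

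**5. How much follow-up could still be recovered?** Trial status gives recruitment from 20 July 2023 to 31 May 2024. Assuming that visit 1 fell on the recruitment date, month-24 visits fall due from 20 July 2025 to 31 May 2026. At the date of version 1-2 (20 March 2025), the first recruit was at 609/30.44 = 20.0 months with one visit left. The last was at 293/30.44 = 9.6 months with three left. These counts apply to that date and shrink with time.

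**The case against.** The strongest reply is that three operative sections agree, including the one devoted to withdrawal, and that item f is a single clause in a list of risks whose purpose is to assure prompt restart. On that view staff would follow the withdrawal section. This limits how likely the harm is. It does not remove the contradiction, because item f states a destination for these patients and makes no exception.

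Other points on that side stand in part.

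- Sampling and the withdrawal section invite patients to stay; they do not oblige them. Only the Group 3 definition states continued monitoring outright.
- A month-24 DXA in a restarter mixes time off and on GH, and it does not measure symptoms. The loss of direct relevance to Group 3's stated purpose is that of the scheduled visits with their questionnaires. The scan still matters as part of the monitoring promised to Group 3.
- Group 3 is already a distinct category, and the exact counting rule for retention may properly sit in an analysis plan that is not shown. The objective is also not confined to one group, so the 2 to 2.5 point figure is as fair as the 4 to 5.

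A reader might infer that the retention and withdrawal rates are therefore unusable, or that restarters have already been lost. The documents support neither. The three-group structure allows restarters who stay to be told apart from leavers, and nothing says which rule has been applied in practice.

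**Conclusion.** The contradiction is real and item f is wrong as written. If it is followed, each restarter loses one to four scheduled post-baseline visits and always the month-24 DXA. The planned observation of symptoms after GH is re-introduced is then lost to the study, apart from clinical follow-up of related adverse events. The total effect cannot be stated without a restart rate.

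The labelling point is secondary. It is a matter of wording that can shift retention by 4 to 5 points per Group 3 member within the discontinuation group, or 2 to 2.5 points over the whole cohort. It is not a missing analysis definition. The per-patient losses rest only on the visit schedule, and the retention shifts only on the planned group sizes.

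**What to change.** 1. **Amend item f** so that restarters resume GH promptly, as now, and are invited, with consent, to continue as Group 3 through month 24, in line with the withdrawal section. Reserve transfer to standard care for those who decline.
2. **Align the wording.** In the Group 3 definition and the withdrawal section, describe people who may stay as withdrawing from the discontinuation group rather than from the study, as the Sampling section already does.
3. **Protect Phase 3.** The second interview group is drawn from those who withdraw from Phase 2, approached when they withdraw. State that Group 3 members remain eligible for those interviews and are approached when they restart GH. Otherwise the rewording in step 2 could drop them from that group.
4. **Report separately** those who restarted GH and those who stopped study visits, with only the latter counting against retention.

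**Cost.** This needs a wording amendment with R&D approval and a notice to the REC (Amendments section), and a check that the information sheets, which are not shown, do not repeat item f. No visits or tests are added beyond those already planned for Group 3. The follow-up change helps only participants with visits left before 31 May 2026. The separate reporting can be settled until Phase 2 analysis begins, four weeks after the last participant's final visit.
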